### Participant timeline

Figure 2 shows details of the schedule of enrolment, intervention and assessment.

**Fig. 2 Fig2:**
[figure not shown]
Participant timeline

### Outcomes

In order to assess the impact of the intervention, key baseline assessment indicators are considered. These include primary and secondary outcomes (Table 2). As the current study aims to optimise the impact of CHW support on individual ART outcomes by stimulating HIV competent households, the primary outcomes for this study are: 1) patient’s viral load and 2) ART adherence (measured by the Adherence to Combination Therapy Questionnaire [31]). Data on ART adherence is collected from the enrolled individual by the research team. In addition, departmental permission has been requested to access the viral load data already collected by the Department of Health. As such, this study only requires secondary access; viral loads will not be collected by the research team.

**Table 2 Tab2:** Outcomes for pre- and postintervention assessment

Primary outcomes	
• Viral load	
• Adherence to antiretroviral treatment	
Secondary outcomes	
Individual-level:	
• HIV knowledge	
• Condom use	
• Quality of life	
• Self-management	
• Disclosure	
• Perceived social support	
Household/-level:	
• HIV knowledge	
• Condom use	
• HIV-related stigma	
• Communication about HIV	
• Household functioning	
• HIV testing	
• Support to a household member living with HIV	

*HIV* human immunodeficiency virus

Moreover, we assess the impact of our intervention on a range of secondary process-related outcomes, measuring both individual outcomes and aspects of HIV competence of the households, which should facilitate individual ART adherence (and thus support the primary outcomes). At the individual level, the PLWH questionnaire assesses HIV knowledge, condom use, quality of life, self-management, perceived social support and disclosure. Outcomes measured at the household level include HIV knowledge, condom use, HIV-related stigma, communication about HIV, household functioning, HIV testing and support to a household member living with HIV. These outcomes are included as indications of household comfort with HIV and communicating about HIV and could be considered as proxy measures for HIV competency at the household level.

### Data collection

Methodologically, this study aims to analyse unique longitudinal data in a partially mixed concurrent equal status design, which involves “conducting a study that has two phases that occur concurrently, so that the quantitative and qualitative phases have approximately equal weight” [32]. Quantitative and qualitative longitudinal methods are both used in order to capitalise on the strengths of each approach. This methodological triangulation increases validity and produces a more comprehensive picture of the studied phenomena. Longitudinal qualitative research can provide explanation for patterns observed in quantitative datasets [33]. The quantitative and qualitative data collection occur simultaneously, but are analysed separately. The findings of both research methods are integrated in the theory formulation phase [32].

#### Quantitative data collection

The quantitative data collection is performed by experienced fieldworkers who have received additional training to sensitise them to the specifics of the study in order to ensure quality and standardisation of the research process. An innovative feature of this cluster-RCT is that one household member of each PLWH enrolled in the study is also interviewed. This enables collection of data on the level of HIV competence within the household (e.g. household functioning, communication, ownership, solidarity, acceptance of outside support). In order to avoid inadvertent disclosure, and to protect patient privacy, the interview with the household member is held at a different time and will be presented as a general health survey. Furthermore, patient and household interviews will be conducted by different interviewers who have experience with this research method in similar research contexts. Small tokens of appreciation in the form of a shopping voucher (for R75 (in the control arm) and R150 (in the intervention arm)) are provided to participants who complete the baseline and follow-up data collection.

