## Methods/design

### Trial design

The primary activity for the Sinako study will be the implementation and assessment of the impact of an HIV competent household intervention. Table 1 represents a schedule of intervention implementation, assessment and dissemination. The intervention will be assessed in a cluster-randomised control trial (RCT) with two arms. CHWs will be the primary actors in this RCT, either continuing to deliver a standard ART adherence support service (arm 1), or a standard ART adherence support service plus a household P^2^CP intervention (arm 2). CHWs, however, are linked to a health care facility, which creates a risk of contamination when CHWs active in different arms operate from the same facility. The facility was therefore selected as the cluster unit of randomisation. The health care facilities in the study setting were categorised as large or small facilities according to the numbers of CHWs employed, which also corresponds to the number of patients. Subsequently, 12 facilities were grouped by selected subdistricts and were randomly selected from the list of facilities for inclusion in the study in arms 1 and – resulting in six facilities or clusters per trial arm. Further blinding of the study arms was not possible because of the clear differences between the intervention and the standard of care. The design and report of this clinical trial protocol follows the Standard Protocol Items: Recommendations for Interventional Trials (SPIRIT) statement (Additional file 1).

**Table 1 Tab1:** Schedule of intervention implementation, assessment and dissemination

	Year 1	Year 2	Year 3	Year 4
Preparatory research activities				
Ethical approval	X			
Preparatory literature review	X			
Quantitative survey development	X			
Mobile data collection tool programming	X			
Qualitative questionnaire development		X		
Development of the household intervention	X	X		
Pilot of the household intervention		X		
Drawing study sample for cluster-RCT		X		
Fieldworker training		X		
Baseline assessment of HIV competence and HIV outcomes				
Baseline quantitative data gathering, capturing and cleaning		X		
Qualitative data collection		X	X	
Baseline quantitative data analysis			X	X
Writing of reports and articles		X	X	X
Implementing the household intervention				
Workshops providing training to CHWs conducting the intervention		X		
Screen participants for eligibility		X		
Informed consent		X		

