### Study setting and site selection

The cluster-RCT will be executed in the Western Cape Province of South Africa in five health subdistricts of the Cape Metro area: Khayelitsha, Klipfontein, Mitchell’s Plain, Eastern and Western.

Mitchell’s Plain has the largest population of the five subdistricts and is predominantly inhabitated by of Coloureds (91%). In contrast, the population in Khayelitsha is mainly Black African (99%). For the three other subdistricts, race distribution is almost equal between Coloureds and Black African populations, with the Western subdistrict showing a significant presence of the White population (29%). All these subdistricts are confronted with severe social and economic challenges, and poverty is widespread. Unemployment is omnipresent with an average unemployment rate of 28.6%, ranging from 18% in Western to 38% in Khayelitsha. Of the five subdistricts, Khayelitsha is the most impoverished, with more than half of the households living in informal dwellings (55%) and with 74% of households surviving on a monthly income of R3200 or less (approximately US$218). Conversely, the Western subdistrict appears to be a little less disadvantaged than the other five subdistricts, with 15% of households living in informal dwellings and a slightly lower unemployment rate of 18% [26].

These social and economic challenges translate into health-related challenges as a result of limited access to health care, education, intra-partner violence, and transactional sex, among others [27]. According to the national antenatal sentinel HIV and syphilis survey, HIV prevalence in the Cape Town metropolitan area, within which the five subdistricts are located, was 21.6% [28]. Moreover, across the entire Western Cape Province, Khayelitsha was identified as having the highest HIV prevalence, with a seroprevalence of 34.3% among pregnant women [29]. With regard to retention in care after 12 months for ART, Eastern performs best of all five subdistricts included in the study at 71.7%, while Klipfontein has demonstrated the least favourable percentage of retention of patients in care, with 61.6% of the patients retained after 12 months. At 48 months of retention in ART care, a similar pattern can be found: Eastern (58.9%); Mitchell’s Plain (58.5%); Klipfontein (56.3%); Western (56.3%); and Khayelitsha (55.0%) [30].

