##### Follow-up data collection

In order to ensure maximum comparability, the postintervention questionnaire collects information on the same outcomes as the baseline questionnaire from the same respondents in both the intervention and control arms of the RCT. The same data gathering procedure will be followed for the post-intervention assessment as for the baseline data collection. If a patient drops out, the research team will try to trace the patient to understand the reason for this loss to follow-up.

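### The survey voucher is R75 in the control arm and R150 in the intervention arm for the same data collection, so payment is fully aligned with arm for survey retention and self-reported adherence

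*Protocol article*

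**What the plan says.** Under Quantitative data collection, the article sets a "shopping voucher (for R75 (in the control arm) and R150 (in the intervention arm"). The vouchers "are provided to participants who complete the baseline and follow-up data collection". The stated condition is therefore survey completion, not attendance at intervention visits.

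The task does not differ by arm. Under Follow-up data collection, the post-intervention questionnaire covers the same outcomes as at baseline, "from the same respondents in both the intervention and control arms of the RCT", and "The same data gathering procedure will be followed for the post-intervention assessment as for the baseline data collection". The description of the intervention visits lists a pill count, a self-management component and a household component for the intervention arm. A voucher is not among them.

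The Outcomes section names two primary outcomes. Adherence is measured by questionnaire: "Data on ART adherence is collected from the enrolled individual by the research team". Viral load is obtained from Department of Health data, and "viral loads will not be collected by the research team". The Sampling section bases the sample size on adherence. The Trial design section says that "Further blinding of the study arms was not possible because of the clear differences between the intervention and the standard of care".

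**The concern.** A payment for completing a survey is an incentive to stay in the study. If it is twice as large in one arm, the arms may differ in who is followed up, for reasons unrelated to the household intervention. In an unblinded trial it might also influence how participants answer. Voucher value is a fixed function of arm, so for retention and questionnaire outcomes the data cannot separate the effect of the payment from that of the intervention. Randomisation does not protect against this, because the difference arises after allocation.

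The exposure matters for two reasons. Adherence is the outcome on which the trial is powered. The plan also allows for heavy loss to follow-up, which leaves room for unequal loss between arms. The household-level and individual-level secondary outcomes are also questionnaire measures and share the problem.

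**Working it through.** **1. The plan's own sample size.** Inputs from the Sampling section: 0.68 versus 0.83, two-sided 5%, 90% power, unpooled Z test, ICC 0.0020, six clusters and 180 individuals per arm (30 per cluster).

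- Variance sum: 0.68×0.32 + 0.83×0.17 = 0.3587.
- n = 0.3587 × (1.960 + 1.282)² / 0.15² = 167.5 per arm.
- Design effect: 1 + (30 − 1)×0.002 = 1.058. Then 167.5 × 1.058 = 177.2, or 6 × 30 = 180 in whole clusters.
- Power at 180 per arm is 0.904.

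The stated 180 reproduces, and equal vouchers would not change it.

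**2. Room for unequal retention.** The plan enrols 320 per arm for 180 needed: 1 − 180/320 = 43.75% loss allowed for, or about 56% retained.

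**3. Selection illustration (assumed rates).** The documents give no retention by arm or by adherence. Take true adherence as 0.68 in both arms. Let control retention be 65% of adherers and 37% of non-adherers, which is 0.68×0.65 + 0.32×0.37 = 56% overall. Observed adherence among completers is p·rA / (p·rA + (1 − p)·rN), where rA and rN are retention in adherers and non-adherers.

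| Arm and retention (adherers / non-adherers) | Overall retention | Observed adherence | Spurious difference |
|---|---|---|---|
| Control, 65% / 37% | 56.0% | 78.9% | reference |
| Intervention, 65% / 50% | 60.2% | 73.4% | −5.5 points |
| Intervention, 75% / 37% | 62.8% | 81.2% | +2.3 points |

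The sign depends on whom the larger voucher retains.

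**4. Reporting illustration (assumed shifts).** True adherence is 0.68 in both arms, reported adherence is 0.68 + s in the intervention arm, with 180 evaluable per arm and design effect 1.058. The standard error is √[(0.68×0.32 + (0.68+s)(0.32−s)) × 1.058/180]. The test is a two-sided t test on 10 degrees of freedom (12 clusters minus 2).

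| s | Standard error | s / standard error | False-positive rate |
|---|---|---|---|
| 0 | 0.0506 | 0 | 5% |
| 2 points | 0.0501 | 0.40 | 6.5% |
| 5 points | 0.0494 | 1.01 | 15% |

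With a normal reference the last two rates are 7% and 17%.

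**5. Value of the voucher.** The only household income figure is for Khayelitsha, described as the most impoverished of the five subdistricts: "74% of households surviving on a monthly income of R3200 or less". Against R3200, R75 is 2.3% and R150 is 4.7%. This gives scale for that subdistrict only.

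**The case against.** The strongest reply is that nothing in the documents shows that a R75 difference changes retention or answers. At the article's own conversion (R3200 for US$218, or R14.68 per dollar) it is about US$5. The voucher rewards completion, not favourable answers. An unblinded arm with seven structured visits already invites favourable self-report, and the voucher's added share cannot be identified. This stands. The rates and shifts above are assumptions, and selection and reporting effects may partly cancel.

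A reader might infer that the trial's result as a whole cannot be interpreted. The documents do not support that, because viral load needs neither a paid survey nor self-report. A reader might also infer that the voucher unmasks fieldworkers. That adds nothing: the trial is unblinded and randomised by facility, the fieldworker accompanies the community health worker to the baseline visit, and the article does not say who hands over the voucher.

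The extra R75 may have been meant to compensate for the longer intervention visits. That is plausible, but the text ties it to data collection.

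Finally, dropouts are to be traced and an attrition analysis is planned. These can describe unequal loss. They cannot separate payment from intervention in the adherence result.

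**Conclusion.** The point holds as an avoidable design inconsistency that should be fixed. Payment for an identical task differs by arm without a stated reason, so it is fully aligned with arm for survey retention and for survey-based outcomes, including the powered adherence outcome.

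That alignment is all the documents establish; they settle neither the size nor the direction of a bias. The rise in the false-positive rate from 5% to about 6.5% to 15% rests wholly on an assumed 2- to 5-point reporting shift with 180 evaluable per arm and the stated ICC. The selection illustration runs from −5.5 to +2.3 points and also rests on assumed rates. Viral load lies outside both routes.

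**What to change.** Pay one voucher value for the same survey in both arms. If intervention participants are to be compensated for their visits, pay that separately and do not make it conditional on outcome assessment.

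Recruitment began on 8 October 2019, so some baseline vouchers may already have been paid. Apply the change to all remaining surveys, above all at follow-up. Raising the control voucher is preferable to cutting the intervention voucher partway through. Record the amounts already paid and report retention by arm. Read the adherence result alongside viral load for everyone enrolled, not only for survey completers.

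Cost: 320 × R75 = R24,000 per paid survey round if every control participant completes (about US$1,635 at the article's conversion), or 180 × R75 = R13,500 if 180 do. An ethics amendment is also needed, and the article names two approving committees. The sample size does not change.

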##### Baseline data collection

For the baseline data collection, the CHW presents the study during the first pre-intervention visit and asks for informed written consent for obtaining contact information of the household members used for the household interview (see section on “Intervention” above). A trained fieldworker joins the CHW during the second preintervention visit. After obtaining informed consent from a PLWH willing to participate in the full study, the fieldworker administers the questionnaire on a hand-held device, using Mobenzi software [34].

##### Follow-up data collection

In order to ensure maximum comparability, the postintervention questionnaire collects information on the same outcomes as the baseline questionnaire from the same respondents in both the intervention and control arms of the RCT. The same data gathering procedure will be followed for the post-intervention assessment as for the baseline data collection. If a patient drops out, the research team will try to trace the patient to understand the reason for this loss to follow-up.

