#### Sampling

A sample size of 180 individuals per arm was obtained by sampling 12 clusters in total (six for each arm) with 90% power to determine an increase in ART adherence (primary outcome (see below)) from 68% to 83% (effect size = 15%) postintervention over a period of 12 months. The proportion in arm 1 (the control group) is assumed to be 0.68 under the null hypothesis and 0.83 under the alternative hypothesis. This sample size has been calculated for a two-sided Z test (unpooled) and 5% significance level. The intracluster correlation is 0.0020. The estimated effect size is conservative since this is a new intervention that has not been rigorously assessed in South Africa. We hope to increase the ART adherence levels by 30%; however, we have powered the study on a lower effect size (15%) to avoid a type 2 error. The total sample size of 640 individuals (320 per arm) instead of 360 (180 per arm) will be used to allow for loss to follow-up. As a result of this oversampling to account for loss to follow-up during the trial, CHW will deliver the intervention to a total of 320 PLWH receiving ART adherence support.

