### Data analyses

#### Quantitative data analysis

The comparison between the two arms using cluster-specific analysis techniques will allow us to assess the net impact of the household intervention on both the primary and secondary outcomes. First, we will perform an intent-to-treat analysis. In a second step, an analysis based on dose-response data will be conducted.

Furthermore, the main relationships between the relevant concepts (household intervention, HIV competence, prevention and treatment outcomes) will be analysed using latent cross-lagged modelling (Mplus). Using chi-square difference testing [36], measurement invariance will be tested to assess whether the latent factors are fully scalar invariant over time (pre- and postintervention). The latent factors will be modelled accordingly in the structural models over time [37]. The analyses will control for demographic and social characteristics, and the medical and medication history of the patient. Furthermore, other quantitative data analysis methods will be used to analyse the baseline and follow-up quantitative data, such as latent cross-lagged modelling, multilevel modelling, logistic regression and Poisson regression, among others. In this way, these results will allow us to successfully reach our research aims, namely to develop and scientifically test the impact of a household intervention on ART outcomes. No missing data are to be expected because of the nature of the Mobenzi data collection tool. To monitor the attrition between the first and second wave, an attrition analysis will be conducted.

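### The article plans to trace drop-outs but states no plan to obtain ART status or the adherence outcome at that contact, while allowing for heavy loss and expecting no missing data

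*Protocol article*

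**What the plan says.** All references are to the protocol article.

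- **Follow-up data collection.** Drop-outs are to be traced: "If a patient drops out, the research team will try to trace the patient to understand the reason for this loss to follow-up". No other use of the contact is described. For the follow-up survey itself, "The same data gathering procedure will be followed for the post-intervention assessment as for the baseline data collection"; at baseline, that means a questionnaire administered by a fieldworker on a hand-held device.
- **Outcomes.** There are two primary outcomes. On adherence: "Data on ART adherence is collected from the enrolled individual by the research team". On viral load: "departmental permission has been requested to access the viral load data already collected by the Department of Health", and "this study only requires secondary access; viral loads will not be collected by the research team".
- **Sampling.** The requirement is 180 per arm; 640 in total "instead of 360 (180 per arm) will be used to allow for loss to follow-up".
- **Quantitative data analysis.** An intention-to-treat analysis comes first, then a dose-response analysis. Attrition between the waves will be analysed. The same section says: "No missing data are to be expected because of the nature of the Mobenzi data collection tool".

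**The concern.** For an adherence outcome, leaving the study can be related to the outcome itself. Some who leave will have stopped ART, and they are the participants whose value most needs to be known. If tracing yields only a reason, they have no adherence value unless that reason happens to reveal one. The comparison then rests on those who were re-interviewed.

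Enrolling more people restores precision. It does not replace the missing values, because the extra participants who stay are not exchangeable with those who left because they stopped treatment.

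Loss could also differ by arm:
- The arms are not blinded.
- The voucher for completing baseline and follow-up is R75 in the control arm and R150 in the intervention arm.
- The intervention encourages participants at every visit to bring a household member or partner, and the article itself describes fear of stigma as a barrier to disclosure. The programme could hold weaker adherers in the study or drive them out, so the direction of bias cannot be predicted.

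**Working it through.** **1. Reproduce the sample size.** Inputs from Sampling: 0.68 vs 0.83, two-sided unpooled Z test, 5% level, 90% power, intracluster correlation 0.0020, six clusters per arm.

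- Before clustering: n = (1.960 + 1.282)² × (0.68×0.32 + 0.83×0.17) / 0.15² = 167.5 per arm.
- Design effect with 30 per cluster: 1 + 29 × 0.002 = 1.058. Then 167.5 × 1.058 = 177.2, met by 6 × 30 = 180. Power at 180 is 90.4%.

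The stated 180 per arm is reproduced.

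**2. Implied loss.** No loss rate is stated. 320 enrolled leaves 180 evaluable if 1 − 180/320 = 43.75% are lost.

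**3. Missing-data sentence against that allowance.** A device can force an answer to each item of an interview that takes place. It cannot produce an interview that does not take place. The sentence and the enlarged sample are therefore compatible only if the sentence refers to items within completed interviews.

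**4. Bias when loss depends on adherence (assumed loss patterns).**

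*No true effect.* 68% adherent in both arms, only non-adherent participants lost:

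| Loss, control | Loss, intervention | Completers, control | Completers, intervention | Apparent effect |
|---|---|---|---|---|
| 10% | 10% | 0.68/0.90 = 0.756 | 0.756 | 0 |
| 10% | 20% | 0.756 | 0.68/0.80 = 0.850 | +9.4 points |
| 20% | 10% | 0.850 | 0.756 | −9.4 points |

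In the second row 288 and 256 of 320 remain. Both exceed 180, so the enlarged sample does what it was meant to do and the bias is still there.

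*True effect as planned.* 0.68 vs 0.83, half of the non-adherent lost in each arm (losses 16% and 8.5%): 0.68/0.84 = 0.810 vs 0.83/0.915 = 0.907. The difference is 9.8 points instead of 15.

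**5. Power cost of counting leavers as failures.** Assume completers at 0.68 vs 0.83, equal loss L in both arms, a share s of the lost counted as non-adherent and the rest like completers. Each proportion is multiplied by (1 − L×s). With 320 per arm the design effect is 1 + (320/6 − 1) × 0.002 = 1.105.

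| L | s | Control | Intervention | Difference | Power |
|---|---|---|---|---|---|
| 0 | – | 0.680 | 0.830 | 15.0 points | 98.9% |
| 20% | all | 0.544 | 0.664 | 12.0 points | 84.5% |
| 43.75% | half | 0.531 | 0.648 | 11.7 points | 82% |
| 43.75% | all | 0.383 | 0.467 | 8.4 points | 54% |

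**The case against.** A reader might infer that no outcome is taken at tracing. The text does not say so. It names one purpose and is silent on the rest, in an article that condenses a fuller protocol; a recorded reason could itself be that ART was stopped.

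A reader might also take the 12-month figures in Study setting and site selection as the rate of missing outcomes: "with 61.6% of the patients retained after 12 months" in Klipfontein, 71.7% in Eastern. These describe retention in ART care across whole subdistricts. The study interview is tied to a home visit or another preferred location, so a patient out of care can still be interviewed and recorded as non-adherent. The trial also recruits patients who have already returned to the clinic and lists several retention measures. Conversely, leaving the study is not stopping ART; the article gives travel out of the province as a cause of attrition.

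Viral load does not depend on the tracing contact, and nothing limits the request for routine data to completers. Intention-to-treat and attrition analyses are named, and the rule for counting drop-outs can be left to an analysis plan. No cut-off behind the 68% and 83% is given, so it cannot be said that stopping ART is a failure by the questionnaire's own definition.

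All of this stands, and it limits the point. Three things remain. An analysis plan cannot recover an ART status that nobody asked for. An attrition analysis describes loss but does not supply outcomes. Viral load is an uncertain substitute, because access had only been requested and a patient out of care may have no test.

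**Conclusion.** The point holds as a gap in stated data collection, joined to an inaccurate sentence about missing data. As written, a drop-out who is not re-interviewed has no adherence outcome, in a trial sized for up to 43.75% loss.

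The size of any bias is unknown. The ±9.4 points rests on assumed losses of 10% and 20% confined to non-adherent participants, and equal loss of that kind under no effect gives no bias. It shows that a modest imbalance could produce nearly two-thirds of the 15-point design difference (9.4/15 = 0.63). It does not show that the result will have the wrong sign, and the article gives no basis for saying so. This is a worthwhile, low-cost improvement and not a fatal flaw.

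**What to change.** 1. **Follow-up data collection.** Have the tracing contact also record current ART status (on ART, stopped or transferred, with date) and offer the adherence questionnaire, by telephone if needed.
2. **Outcomes.** State that the routine viral load request covers every enrolled participant who has not withdrawn data consent, and add the date of last ART collection or visit.
3. **Quantitative data analysis.** Replace the no-missing-data sentence with an acknowledgement that interviews will be missed.
4. **Counting rule.** Analyse participants documented as having stopped ART as not adherent, with transfers not counted as stopping. Do this in the primary analysis or at least as a pre-specified sensitivity analysis.

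**Cost.** A few questions at a contact already planned and a somewhat wider data request. Telephone contact needs the same care against inadvertent disclosure that the article applies to household interviews. Reported adherence will be lower in both arms. If many leavers count as failures, the difference and the power fall: at 43.75% loss and 320 per arm, to about 54% if all the lost count as non-adherent and 82% if half do. That is a reason to record true status rather than to assume it.
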